#### Participants

Overweight or obese (BMI between 25 and 40 kg/m^2^) fathers (aged 18-65 years) with a child aged between 5 and 12 years of age (i.e. primary school age) will be recruited from the local communities using the following strategies: local media releases (print, TV and radio), school newsletters items, school-based presentations, fliers distributed through community notice boards and local businesses, paid advertisements in local newspapers, local networks of sports clubs, service clubs, local government, and community health facilities. Fathers will be screened for eligibility via telephone. Ethics approval has been obtained from the University of Newcastle Human Research Ethics Committee. Written informed consent will be obtained from the fathers prior to their participation as well as child assent.

Fifty fathers will be recruited from one LGA (Maitland) and randomized to either the HDHK program or a 6-month wait-list control group. Fathers (and their children) will be stratified by BMI category (overweight [25-29.9 kg/m^2^], obese class 1 [30-34.9 kg/m^2^], obese class 2 [35-40 kg/m^2^]) and randomized using a computer-based random number-producing algorithm, to intervention or control group. To ensure concealment, the sequence will be generated by a statistician and given to the project manager. Randomization will be completed by a research assistant not involved in assessments and the allocation sequence will be concealed when enrolling participants. Fathers and their children will be assessed at baseline, post-intervention (3-months) and 6-months (3-months post-intervention).

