#### Sample size

For the RCT, based on 80% power to detect a significant weight loss difference between groups of 3 kg, assuming SD = 5 (*P *= 0.05, two-sided) a sample size of 20 fathers for each group will be needed at 6 months. Assuming a 20% attrition rate [14], a total sample of 50 fathers will be required. Participants will be blind to group allocation at baseline assessment. Once baseline assessments are completed, participants will receive a sealed envelope with a note advising their group allocation. The wait-list control group will receive no information or intervention before attending the 3- and 6-month follow-up assessment sessions. There will be a 6-month wait-list control group as (a) ethically every overweight man is deserving of an intervention and is unlikely to remain weight stable; (b) randomization to 'no' intervention for a greater length of time is unlikely to be acceptable and is likely to lead to high attrition compromising study integrity.

Stage 3 - Community effectiveness trial design

When translating evidence-based programs into real-world settings, ongoing modifications are required based on the unique characteristics of the settings and populations. Modifications will be made to the program based on both outcome and process evaluation from the community RCT and each subsequent program implementation in 2011 and these will be documented. The goal will be to develop a comprehensive model of a real-world intervention for application in communities through updating materials, developing standardized train-the-trainer education and resources and ongoing evaluation of the implementation of the intervention with a final evaluation conducted in 2012.

The HDHK program will be evaluated for effectiveness in the community roll-out using a non-randomized, prospective design. This evaluation will be conducted in both 2011 and 2012 in the five local government areas. The exclusion criteria is minimal to align with a true translational model and will only include BMI < 25 or lack of doctor's approval. Measures (detailed below) will be collected at baseline, post-intervention, and 6 and 12 months post-baseline. We aim to recruit 15-20 fathers from each area. Results from each program will be pooled and it is expected at least 200 families will participate in the community trial of the HDHK program.

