#### Primary outcome measure

The primary outcome measure is body weight of the fathers at 6-month follow-up. Weight will be measured with fathers wearing light clothing, without shoes on a digital scale to 0.1 kg (model CH-150 kp, A&D Mercury Pty Ltd, Australia). Weight will be recorded twice and the average of the two measures reported. The same protocol will be followed to record children's weight.

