### Data Analysis

Analyses will be performed using PASW Statistics 19 (SPSS Inc. Chicago, IL). Data will be presented as mean (SD) for continuous variables and counts (percentages) for categorical variables. Characteristics of completers versus dropouts will be tested using independent *t *tests for continuous variables and chi-squared (χ^2^) tests for categorical variables. The significance level will be set at 0.05 for all analyses. Analyses will be performed separately for fathers and children and included all randomized participants. Generalized linear mixed models (GLM) will be fitted with an unstructured covariance structure for all primary and secondary outcomes. Differences between means and 95% confidence intervals (CIs) will be determined using GLM.

GLM will be used to assess all outcomes for the impact of group (Intervention and control), time (treated as categorical with levels baseline, 3-months and 6-months) and the group-by-time interaction, these three terms forming the base model. Baseline scores for subjects who dropped out at 3-months and/or 6-months will be retained consistent with an intention-to-treat (ITT) analysis. Mixed models are more robust to the biases of missing data, and provide better control of Type 1 and Type 2 errors than last observation carried forward (LOCF) in Analysis of Variance [70]. Similarly, imputation methods such as LOCF or baseline carried forward may bias results towards the null in obesity trials where untreated overweight men are likely to increase their weight. Age, SES and sex of the child will be examined as covariates to determine if they contributed significantly to the models. If a covariate is significant, two-way interactions with time and treatment will also be examined and all significant terms will be added to the final model to adjust the results for these effects. Effect sizes will be determined using Cohen's *d *[71] and calculated using mean differences and the pooled standard deviation of the group (*d *= M_1 _- M_2_/σ_pooled_). We will also examine a range of secondary outcomes to support the primary outcome (e.g. reduction in waist circumference, increase in physical activity, reduction in kilojoule intake). Additional exploratory models will be fitted to examine if the fathers who have the greatest reduction in weight are also those who have the greatest improvements in the secondary outcomes.

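### Randomisation is stratified by father's BMI category, but the analysis model leaves that factor out, so analysis and design do not match and some precision may be lost

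*Protocol article*

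**What the plan says.** - **Allocation** (Participants, Stage 2): "Fathers (and their children) will be stratified by BMI category", in three classes: 25-29.9, 30-34.9 and 35-40 kg/m². Allocation then follows a computer-generated random sequence. The article does not say whether blocks are used within strata.
- **Model** (Data Analysis): a mixed model with unstructured covariance. Its fixed terms are group, time (baseline, 3 and 6 months) and "the group-by-time interaction, these three terms forming the base model".
- **Covariates** (Data Analysis): "Age, SES and sex of the child will be examined as covariates", and they stay only if significant. BMI category is not named.
- **Outcome** (Primary outcome measure): "The primary outcome measure is body weight of the fathers at 6-month follow-up".
- **Sample size**: the calculation is "based on 80% power to detect a significant weight loss difference between groups of 3 kg", with SD 5 and P = "0.05, two-sided", and concludes that "a sample size of 20 fathers for each group will be needed at 6 months". It adds: "Assuming a 20% attrition rate [14], a total sample of 50 fathers will be required".

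**The concern.** A factor used to restrict randomisation normally goes into the analysis. If it predicts the outcome, fitting it removes variance from the treatment comparison. If it is left out of a trial whose arms were kept balanced on it, the model's standard error includes variation that the design has already removed.

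This is more than detail that an article might leave to an analysis plan. The text states which terms form the base model, which covariates are eligible and how they are retained. Under that rule the child's sex may enter a model of the father's weight, while the one factor that governed allocation may not. With about 40 fathers expected at 6 months, any loss of precision matters.

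**Working it through.** **Inputs.** From the article: difference 3 kg, SD 5 kg (read as the SD of weight change, because the calculation concerns weight loss), two-sided 0.05, 20 per group at 6 months, three strata. Not in the article: R², the share of variance in weight change explained by BMI category. It is assumed to lie between 0 and 0.20.

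**1. The plan's own figure.** n per group = 2 × (1.960 + 0.842)² × 5² / 3² = 43.6, so 44 (45 with the t distribution). The stated 20 does not reproduce; the attrition step does (40 / 0.8 = 50). At 20 per group the standard error is 5 × √(2/20) = 1.58 kg, the noncentrality is 3 / 1.58 = 1.90, and t power on 38 df is 45.6%. This shortfall is a separate matter. It is shown only to set the baseline.

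**2. Which term helps.** Baseline is a level of time, so the change from baseline to 6 months already removes differences in weight level between strata. In simulations of 40 fathers (600 trials per scenario, complete data, unstructured covariance), adding BMI category as a main effect left the group-by-time estimate the same to rounding error. The standard error was also the same (for example 1.559 kg in both models). Only BMI category × time can change this contrast.

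**3. Size of the gain.** With BMI category × time fitted, the residual SD of change is 5 × √(1 − R²) on 36 df, and the 95% half-width is t(0.975, 36) × residual SD × √(2/20).

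| Model | Residual SD (kg) | 95% half-width (kg) | t power |
|---|---|---|---|
| BMI category omitted (38 df) | 5.00 | 3.20 | 45.6% |
| Fitted, R² = 0 | 5.00 | 3.21 | 45.5% |
| Fitted, R² = 0.05 | 4.87 | 3.13 | 47.4% |
| Fitted, R² = 0.10 | 4.74 | 3.04 | 49.5% |
| Fitted, R² = 0.20 | 4.47 | 2.87 | 54.2% |

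Leaving df aside, the unadjusted standard error exceeds the adjusted one by 1/√(1 − R²) − 1, which is 2.6%, 5.4% and 11.8% at R² = 0.05, 0.10 and 0.20.

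**4. Test size when the factor is omitted.** If the arms are balanced exactly within strata, the true size of a nominal 5% test is 2 × [1 − Φ(1.96/√(1 − R²))], giving 4.4%, 3.9% and 2.8% at the same R² values. That balance is an assumption. Simulating 50 fathers with 20% random dropout and assumed strata shares of 33/42/25%:

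- Simple randomisation within strata gave about 5% at every R².
- Blocks of 4 gave about 4.7%, 4.2% and 3.3%.

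The unadjusted test is therefore conservative only if something like blocking is used.

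**The case against.** The strongest reply is that the effect of interest is change, and the model already handles weight level. BMI category plainly predicts how heavy a father is, but nothing in the article shows that it predicts how much he loses. At R² = 0 the adjustment gains nothing, and up to R² = 0.10 it adds at most about 4 points of power and 0.16 kg of half-width. This stands, and it is why the loss can only be stated conditionally.

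Two stronger readings are tempting, and neither is supported:

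- **That intervals are certainly too wide and the tests certainly conservative.** The first needs R² above zero, and the second also needs balance within strata. The article reports neither.
- **That the loss is large because strata explain much of the variance in weight.** A reader might infer this because the primary outcome is worded as weight at 6 months. If plain 6-month means were compared, the simulated standard error would be about 5.1 kg unadjusted against 3.2 kg adjusted. Those figures rest on assumed stratum mean weights of 88, 103 and 120 kg. The Data Analysis section does not name the contrast outright, but it includes baseline as a level of time with a group-by-time term, and the sample size is set on weight loss. Both point to change.

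It is also fair to say that the power shortfall comes from the sample size calculation, not from this omission. Even at R² = 0.20, fitting BMI category reaches only 54.2%.

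**Conclusion.** The mismatch is real and follows from the stated rule: the stratification factor is neither in the base model nor eligible to enter it. For the group-by-time contrast in fathers' weight the consequence runs from none to modest. Over an assumed R² of 0 to 0.20, fitting the factor changes power by between −0.1 and +8.6 points (45.6% to 45.5% or 54.2%). It changes the half-width by between +0.01 and −0.33 kg (3.20 kg to 3.21 or 2.87 kg). These figures assume 20 fathers per group at 6 months, a 3 kg difference and an SD of change of 5 kg.

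Any error in test size from the omission is on the conservative side, so a positive result would remain valid. Severity is minor to moderate. The point is worth acting on because the remedy costs almost nothing and the trial has little precision to spare.

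**What to change.** In the primary model for fathers' weight, add BMI category at randomisation and BMI category × time as fixed effects, kept whatever their significance. Do the same, preferably, for the other outcomes of the randomised stage. The gain there is unknown, because the article gives nothing on whether the father's BMI category predicts them. State also whether allocation is blocked within strata, since that decides whether the unadjusted test would be conservative.

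The cost is one line of model syntax and six fixed-effect parameters (2 for the main effect and 2 × 2 for the interaction with three time points). For the change contrast this takes residual df from 38 to 36. If BMI category does not predict change, the half-width grows by only 0.01 kg. The variable must already be recorded for randomisation, so no new data are needed.

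### Covariates and their interactions enter the RCT's final model only if significant, so the primary estimate comes from a model chosen on the outcome data

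*Protocol article*

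**What the plan says.** All of this stands in the Data Analysis section of the protocol article unless noted.

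- The mixed model is "fitted with an unstructured covariance structure for all primary and secondary outcomes". Its fixed effects are group, "time (treated as categorical with levels baseline, 3-months and 6-months) and the group-by-time interaction, these three terms forming the base model".
- Covariates are then screened: "Age, SES and sex of the child will be examined as covariates to determine if they contributed significantly to the models". For any that pass, "two-way interactions with time and treatment will also be examined and all significant terms will be added to the final model".
- One threshold is given: "The significance level will be set at 0.05 for all analyses".
- On the analysis set: "Analyses will be performed separately for fathers and children and included all randomized participants".
- Under Primary outcome measure: "The primary outcome measure is body weight of the fathers at 6-month follow-up". The Sample size section frames the target as a difference in weight loss: "based on 80% power to detect a significant weight loss difference between groups of 3 kg".

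No sentence makes the base model the primary analysis, or the adjusted model a sensitivity or exploratory one. The Participants section stratifies randomization by BMI category, but that factor is neither in the base model nor among the candidates.

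**The concern.** The candidates are named in advance, but the model is not. The outcome data decide which terms enter, and they decide again for each outcome. The model that results is the one called final, so on the wording it supplies the headline result. A reader of the trial report could not tell from the protocol which model was meant to give the primary estimate, and two outcomes could carry differently adjusted effects for no reason but chance. The interval is computed as if the chosen model had been fixed from the start.

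This is a stated rule, not a detail left to a later document. An analysis plan could cure it only by overriding the rule.

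**Working it through.** **Inputs from the protocol.** Sample size section: target 3 kg, SD 5 kg, two-sided 0.05, 20 per group at 6 months, 20% attrition, 50 fathers. Data Analysis section: three visits, unstructured covariance, three candidates, threshold 0.05.

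The step from 40 to 50 reproduces: 40 / 0.8 = 50. The 20 per group does not: 2 × (1.960 + 0.842)² × 5² / 3² = 43.6, so 44 per group. That is a separate matter; only the planned trial size is used here.

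**Assumptions not in the protocol.** Baseline weight SD 14 kg. The SD of 5 kg is read as the SD of 6-month change. One candidate correlates 0 to 0.5 with both baseline weight and change; the other two are unrelated. 25 per arm, 20% missing at 6 months. The candidates are tested together, then the interactions of those kept. There is no treatment effect.

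**Step 1: chance of a false entry.** With three unrelated candidates, 1 − 0.95³ = 14.3%. The simulation gives 18.7%, so its approximate tests run somewhat liberal and the entry rates below lean high.

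**Step 2: which terms can move which contrast.** Let C be the covariate and G the group. Add γC (main effect), θCG (covariate-by-treatment) and λₜC (covariate-by-time) to the base model. In the change from baseline to 6 months, γC and θCG cancel, leaving δ₆G + λ₆C. So with complete data only a covariate-by-time term alters the group-by-time estimate δ₆. When a covariate-by-treatment term is forced in with 20% missing at 6 months, the estimate moves by roughly 0.1 kg or less on average and its SE is essentially unchanged.

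The 6-month level difference is β_G + δ₆ + θC, where β_G is the group term. Once θ is kept, it depends on C.

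**Step 3: expected size of the shift.** Shift ≈ λ₆ × (difference in mean C between groups). With C in SD units, λ₆ = 5r for correlation r. The mean difference has SD √(2/25) = 0.283 with 25 per group, or √(2/20) = 0.316 with 20. The mean absolute shift is √(2/π) = 0.798 times that:

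- r = 0.3: 0.34 to 0.38 kg
- r = 0.4: 0.45 to 0.50 kg
- r = 0.5: 0.56 to 0.63 kg

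**Step 4: simulation of the stated procedure** (1,500 runs per row, 6-month change contrast).

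| r | Any covariate kept | By-time term kept | By-treatment term kept | Type I, base | Type I, selected | Mean shift when by-time kept | All runs with shift > 0.5 kg |
|---|---|---|---|---|---|---|---|
| 0 | 18.7% | 2.1% | 1.1% | 4.9% | 4.9% | 0.34 kg | 0.5% |
| 0.3 | 65.1% | 30.8% | 4.9% | 4.7% | 4.9% | 0.45 kg | 11.7% |
| 0.4 | 83.1% | 61.8% | 6.9% | 5.1% | 5.7% | 0.50 kg | 25.9% |
| 0.5 | 95.0% | 88.5% | 7.7% | 4.9% | 5.4% | 0.59 kg | 41.8% |

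The simulated shifts agree with step 3. They are higher at r = 0.3, where only the larger estimated slopes pass the screen. The base SE is 1.50 to 1.54 kg. The largest single shift was 3.9 kg, at r = 0.5. The Monte Carlo SE of a rejection rate is √(0.05 × 0.95 / 1,500) = 0.6 points.

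**Step 5: level difference at 6 months.** In row order, type I error is 5.1, 5.2, 4.9 and 5.9% for the base model and 5.7, 5.9, 6.7 and 5.6% after selection. When any covariate is kept, the estimate moves by 1.10, 1.43, 1.78 and 2.12 kg on average. For scale, with uncorrelated covariates and complete data its SE is about √(14² + 5²) × 0.283 = 4.2 kg.

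**The case against.** The best defence is that the selection is bounded: three named candidates, a stated sequence and one threshold. In a randomized trial with a continuous outcome, linear models with or without baseline covariates or covariate-by-time terms target the same average effect. The error rate stays close to nominal, and the typical shift is under half a standard error. All of that stands. It limits the size of the problem, but it does not tell the analyst which model gives the primary result.

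Three stronger readings are tempting, and the documents do not support them.

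- *A retained treatment-by-covariate term turns the treatment effect into the effect at age zero, with a hugely inflated SE.* That happens to the group term in a change-score regression with uncentred covariates, where one can obtain rejection rates of 7.5 to 9.1% and SEs of 9 to 10 kg. The protocol plans a three-visit model in which group-by-time carries the effect on change. It reports differences between means, and it nowhere says that covariates are left uncentred.
- *The selection takes place in about 40 completers.* Forty is the number planned to have a 6-month weight. The model includes all randomized fathers, 50 as planned.
- *Type I error is materially out of control and the interval clearly invalid.* For the change contrast, the highest rejection rate after selection is 5.7%. With a true effect of zero that is 94.3% coverage, within about one Monte Carlo SE of 95% (0.7 against 0.6 points).

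**Conclusion.** The concern holds as a defect of specification. The primary estimate is left to an outcome-driven screen, and no model is designated primary.

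The consequence lies mainly in the estimate. At assumed correlations of 0.3 to 0.5, a retained covariate-by-time term shifts the 6-month group-by-time estimate by 0.45 to 0.59 kg on average. That is 15 to 20% of the 3 kg target (0.45/3 and 0.59/3) and about 0.3 to 0.4 of an SE (0.45/1.54 and 0.59/1.50). If all candidates are unrelated to weight, such a term seldom enters (2.1% of runs) and the issue is minor.

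The estimand itself is at risk only for the level difference, when a covariate-by-treatment term is kept (1.1 to 7.7% of runs). That difference then needs a stated covariate value, and the protocol gives none. All sizes rest on the assumed SDs and correlations; the wording defect does not.

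**What to change.** Name one primary model for the RCT in advance: group, time and group-by-time, plus the BMI category used to stratify randomization. State for age, SES and, for child outcomes, child sex whether each is always included and centred or always excluded. Delete the step that adds terms because they are significant. Report covariate-by-treatment interactions only as exploratory analyses that do not replace the primary estimate.

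By step 2 of the working, a main effect alone hardly touches the change contrast. The text should therefore also say whether BMI category and any fixed covariate enter with their product with time.

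The change is wording only. BMI category costs two degrees of freedom (three levels less one), and age, SES and child sex at most three if each enters as a single term. Products with time add two for each of these. The drawback is that some may go to covariates of little prognostic value.

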**Methods/Design:**

The Healthy Dads, Healthy Kids community trial consists of three stages: (i) *Stage 1 - program refinement and resource development *(ii) *Stage 2 - community randomized controlled trial *(iii) *Stage 3 - community effectiveness trial*. The program will be evaluated in five Local Government Areas in the Hunter Valley Region of NSW, Australia. For the community randomized controlled trial, 50 overweight/obese men (aged 18-65 years) from one Local Government Area with a child aged between 5-12 years of age will be recruited. Families will be randomized to either the program or a 6-month wait-list control group. Fathers and their children will be assessed at baseline, post-intervention (3-months) and 6-months. Inclusion criteria are: body mass index 25-40 kg/m^2^; no participation in other weight loss programs during the study; pass a health-screening questionnaire; and access to a computer with Internet facilities. In the community trial, the program will be evaluated using a non-randomized, prospective design in five Local Government Areas. The exclusion criteria is body mass index < 25 kg/m^2 ^or lack of doctor's approval. Measures will be collected at baseline, 3-, 6- and 12-months. The program involves fathers attending seven face-to-face group sessions (three with children) over 3-months. *Measures*: The primary outcome is fathers' weight. Secondary outcomes for both fathers and children include: waist circumference, blood pressure, resting heart rate, physical activity, sedentary behaviors and dietary intake. Father-only measures include portion size, alcohol consumption, parenting for physical activity and nutrition and parental engagement. Process evaluation will determine the fidelity, dose (delivered and received), reach, recruitment and context of the program.

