For the community trial, the mean change between pre and post-intervention outcomes will be analyzed using paired Student's t-test when change data are normally distributed. Wilcoxon matched pairs signed rank tests will be used for non-parametric tests. Per protocol analyses for both the RCT and the community trial will be performed for those who attended at least 70% of HDHK sessions and the follow-up assessment visits.

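### Stage 3 is analysed only by a paired pre/post test, which leaves 6 and 12 months without a stated analysis or, read loosely, restricts each to the fathers who attended

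*Protocol article*

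**What the plan says.** Stage 3 is an uncontrolled roll-out: "The HDHK program will be evaluated for effectiveness in the community roll-out using a non-randomized, prospective design" (Stage 3 design text, under the Sample size heading). Its visits are given in the same place: "Measures (detailed below) will be collected at baseline, post-intervention, and 6 and 12 months post-baseline". The Abstract has the same schedule: "Measures will be collected at baseline, 3-, 6- and 12-months".

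On the outcome, the Primary outcome measure section states: "The primary outcome measure is body weight of the fathers at 6-month follow-up". It does not confine this to the RCT.

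The Data Analysis section fixes the Stage 3 method: "the mean change between pre and post-intervention outcomes will be analyzed using paired Student's t-test when change data are normally distributed", and "Wilcoxon matched pairs signed rank tests will be used for non-parametric tests". It adds a per-protocol analysis for both stages, limited to fathers who met an attendance threshold of 70% of sessions and came to follow-up. No time point or model is named for it.

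The same section specifies a mixed model with an unstructured covariance. Its base terms are group, time (baseline, 3 and 6 months) and their interaction, and it covers everyone randomized. One reason given for it is: "Mixed models are more robust to the biases of missing data".

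**The concern.** Stage 3 is the largest part of the project (at least 200 families expected, against 50 fathers in the RCT), has the fewest exclusions, and is the only stage followed to 12 months. The Background justifies the project partly by the need for longer follow-up. The one main analysis named for this stage compares baseline with the end of the programme.

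Two things are at stake. First, the later visits may be analysed in whatever way is chosen after the data are seen, or reported without a planned contrast. Second, if the paired test is simply repeated at 6 and 12 months, each result describes only those who returned. With no control arm, any link between weight change and returning passes directly into the reported effect. If fathers who do less well tend not to return, the mean loss is overstated.

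**Working it through.** **1. What does *post-intervention* mean here?** The Abstract and the Stage 2 Participants section both equate it with 3 months. The Stage 3 visit schedule lists it as a separate item before 6 and 12 months. By the article's own usage, the paired test is a 3-month test.

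**2. Can the mixed model cover Stage 3?** Not as written.

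| Feature | Mixed model in Data Analysis | Stage 3 |
|---|---|---|
| Group term | Intervention versus control | One arm |
| Time levels | Baseline, 3, 6 months | Baseline, 3, 6, 12 months |
| Population | All randomized | Nobody randomized |

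**3. What follows under each reading?**

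- Strict: the test uses baseline and 3 months. It loses only fathers who miss the 3-month visit. Weights at 6 and 12 months have no stated analysis.
- Loose: the test is repeated at each visit. Both named tests need both values of a pair, so each visit keeps only its attenders. The per-protocol analysis restricts further.

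Under neither reading does a stated Stage 3 effect analysis retain fathers with incomplete follow-up.

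**4. Size of the completer bias.** Let *d* be the fraction lost, *C* the mean change in completers and *D* the mean change in those lost. The all-father mean is (1 − d)C + dD, so

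completer mean − all-father mean = d(C − D).

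The article states neither *d* nor *C − D* for Stage 3. Both are assumed below; entries are kg of overstated loss.

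| d | gap 1 kg | gap 4 kg |
|---|---|---|
| 10% | 0.1 | 0.4 |
| 20% | 0.2 | 0.8 |
| 30% | 0.3 | 1.2 |
| 40% | 0.4 | 1.6 |

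**5. Is it a matter of power?** No. With 200 fathers, complete pairs number 200(1 − d) = 180, 160, 140 and 120. Borrowing the RCT's SD of 5 kg as an assumption, the change detectable with 80% power at two-sided 0.05 is 5 × (1.960 + 0.842)/√n = 1.04, 1.11, 1.18 and 1.28 kg.

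**6. What would a mixed model recover?** A simulation used assumed values throughout: 3-month change with mean −5 kg and SD 5; 12-month change = −4 + 0.8 × (3-month change + 5) plus noise of SD 3; and dropout before 12 months more likely in fathers who had lost less at 3 months (logistic, slope 0.2 per kg). The true 12-month mean was −4.0 kg.

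| Dropout | Completers only | Using 3-month values |
|---|---|---|
| 20% | −4.7 | −4.0 |
| 30% | −5.0 | −4.0 |
| 40% | −5.3 | −4.0 |

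The last column predicts 12-month change by regression on 3-month change, as a stand-in for the likelihood analysis. It recovers the truth because dropout was built to depend only on an observed weight.

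**7. Where it would not help.** For fathers with a baseline weight only, the model's 3-month mean is the completers' 3-month mean + β × (baseline mean of all fathers − baseline mean of completers), where β is the slope of 3-month on baseline weight. If baseline weight does not differ between those who return and those who do not, the correction is zero and the estimated change equals the completer change.

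**The case against.** The strongest reply is that this is a condensed article and the later visits may be analysed in a fuller plan. The per-protocol sentence mentions follow-up visits for the community trial too, so *post-intervention* may be meant loosely. That is possible, and nobody should infer that the 6- and 12-month data will go unanalysed. But the article does not merely stay silent: it names the Stage 3 test, and on the loose reading that test has the missing-data weakness the article itself argues against. It could also be said that 6 months is primary only for the RCT. The text does not say so, and the 12-month visit would still lack an analysis.

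A second reply is that dropout is described: completers are compared with dropouts, and 6-month retention is a feasibility measure. This shows the loss but does not adjust for it.

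A third is that Stage 3's main limitation is the absence of a control group, and that the controlled estimate comes from the RCT, which does use the mixed model. This stands, and it lowers the severity.

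Several stronger readings are tempting but unsupported:

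- That the test drops every father lost to follow-up. A strict 3-month test drops only those missing that visit.
- That the bias can be computed from the article's 20% attrition and set against 3 kg. Both belong to the RCT; the 3 kg is a between-group difference, and Stage 3 states no target.
- That a signed-rank test removes the mean-change estimate. The section says continuous data will be presented as mean (SD), and choosing a test does not prevent that.
- That carrying baseline forward would be a conservative check. The section argues against that method, and it is not conservative if fathers who leave gain weight.

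**Conclusion.** The point holds as a should-fix. The stated Stage 3 analysis either stops at 3 months, short of the 6-month primary time point and the 12-month follow-up, or uses only the fathers present at each visit, contrary to the section's own argument for mixed models.

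The direction of bias (overstated loss) rests on the assumption that fathers who do less well are less likely to return. The size is hypothetical: 0.1-1.6 kg over the assumed ranges, with nothing in the article to narrow it. A reader might infer that a mixed model would remove the bias. It does so only where dropout is explained by weights already observed, so the gain is mainly at 6 and 12 months for fathers with an earlier follow-up weight.

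**What to change.** Replace the Stage 3 paired tests with a linear mixed model for weight with time as the only fixed factor (categorical: baseline, 3, 6 and 12 months), an unstructured covariance, and all fathers with a baseline weight. Report mean change from baseline with a 95% CI at each visit, naming 6 months as the primary contrast and 12 months as maintenance. This is the RCT model without its group terms and with a 12-month level added.

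State in the same paragraph that the model assumes data missing at random, that fathers with only a baseline weight add little, and that the result is an uncontrolled change. The planned comparison of completers with dropouts can stay as supporting description.

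The cost is a few sentences and a little more analysis work. The data are already to be collected and no new measurements are needed. The reported change may be less favourable than the completer figure.
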